#### Perspective

The aim of the economic evaluation is to inform health service decision makers about the costs, outcomes, economic efficiencies and budget impact of introducing task-shared psychosocial counselling to their chronic disease patient body in a resource-scarce context. As such, the economic evaluation will be conducted from a provider perspective, reflecting health service budget constraints. In line with good practice recommendations, the analyses will also be presented from a societal perspective (including both provider and patient perspectives). While public sector primary healthcare is free at the point of use, patients incur time and travel costs when accessing care and may experience productivity losses; in addition, they may incur costs when using private sector health services. These costs will be collected to inform the patient perspective within the economic evaluation.

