### MIND economic evaluation

#### Objective

The study will be a prospective economic evaluation. The objectives include estimating:Full economic provider costs of the mental health intervention; any cost offsets attributable to the intervention related to changes to the costs of HIV or diabetes care at the primary care level and changes to the costs of referral care (including tuberculosis (TB), emergency department and inpatient care).Patient costs: associated with the intervention which will include direct out-of-pocket payments to private health providers (consultations and medications, etc), travel and subsistence costs and productivity losses.Cost-effectiveness in terms of the incremental cost per unit of improvement in disease-specific outcome (CES-D, AUDIT, HIV-1 RNA, HbA1c).Cost-utility in terms of the incremental cost per quality-adjusted life year (QALY) gained.Budget impact of scaling up the intervention.

To achieve these objectives, the incremental cost-effectiveness ratio (ICER) will be calculated by ordering the MIND_DED, the MIND_DES and MIND_TAU alternatives from least cost to highest cost and calculating the difference in costs and outcomes against the next less costly, non-dominated alternative or against the common baseline of MIND_TAU.

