Vehicles	Vehicles used for HIV/diabetes service	Inventory	Replacement value converted to annual equivalent cost	HIV/Diabetes headcount
Recurrent costs				
HIV/Diabetes personnel	Number of staff and staff time spent on HIV/diabetes service	Time from facility data	Cost of employment ×proportion of time	HIV/Diabetes headcount
Drugs	ARV/Diabetes medication	Treatment protocol	National tender prices	Direct allocation
Diagnostic tests	CD4 test, diabetes monitoring tests, etc	Treatment protocol	National Health Laboratory Service prices	Direct allocation
Non-HIV/diabetes personnel	Managerial, cleaning and security staff	Facility utilisation	Facility expenditure	Facility headcount
Building operating and maintenance	Electricity, water, other utilities, phone, cleaning, transport and stationery	Facility utilisation	Facility expenditure	Facility headcount
Other related healthcare providers				
Public clinic visit	Average cost per visit	Patient interviews	Facility expenditure	Facility headcount
Public hospital ER/OPD visit	Average cost per OPD visit	Patient interviews	Facility expenditure	Facility Inpatient days and Outpatient headcount
Public hospital inpatient day	Average cost per inpatient day	Patient interviews	Facility expenditure	Facility Inpatient days and Outpatient headcount

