### Estimating costs for the patient perspective

#### Measurement of resource use

For the patient perspective, we will use a questionnaire at baseline, 6 and 12 months to estimate resource use. This will capture any user fees associated with public, private or NGO-provided health services as well as traditional and faith-based therapies. In addition, we will ask patients to estimate their time spent accessing healthcare services, as well as out-of-pocket payments for transport, subsistence and accommodation. Travel, subsistence and accommodation costs will relate to both the patient and their caregiver, if the patient is accompanied by a caregiver to any of these services.

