#### Determining cost-effectiveness

The analysis will be conducted in line with the Consolidated Health Economic Evaluation Reporting Standards guidelines.^47^ Decision analytical models^37^ integrating the cost and outcomes of the different intervention alternatives will be developed to assess cost-effectiveness. As a meaningful impact of the MIND-DES and MIND-DED on both costs and effects is anticipated, ICERs will be estimated in terms of incremental cost per natural unit and/or intermediate outcome for the CEA, and incremental cost per QALY gained for the CUA. As the trial is focused on health systems strengthening for the delivery of mental health services, the decision rule applies to maximising health within the healthcare budget constraint. Therefore, ICERs will be calculated from the provider perspective and, the cost per QALY gained will be compared with the cost-effectiveness thresholds (CETs) for LMIC settings.^48^ If our intervention’s ICER is less than the chosen CET, this will mean that diverting resources to the intervention will increase population health, and if the ICER is more than the CET the intervention is not cost-effective. Patient costs will be collected and reported on separately. In addition, to satisfy the requirements of common guidelines^47^ and to allow for some degree of comparability with other studies, the ICERs will also be presented for the societal perspective, that is, including both provider and patient costs.

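### As written, the societal ICER would add user fees paid to public hospitals to provider costs that already cover the same care, and the sections disagree on whether public fees are a patient cost

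*Protocol article*

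**What the plan says.** Four parts of the protocol article bear on this.

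- **Summation.** Under Perspective, "the analyses will also be presented from a societal perspective (including both provider and patient perspectives"). Under Determining cost-effectiveness, "the ICERs will also be presented for the societal perspective, that is, including both provider and patient costs". Neither place mentions transfers between patient and provider.
- **Provider cost.** In Table 1, under other related healthcare providers, public clinic visits, hospital ER/OPD visits and inpatient days are each costed at a unit average, for example "Average cost per inpatient day". The valuation source is facility expenditure. No fee income is deducted.
- **Patient cost, wide version.** Under Estimating costs for the patient perspective, Measurement of resource use, the questionnaire is described thus: "This will capture any user fees associated with public, private or NGO-provided health services as well as traditional and faith-based therapies".
- **Patient cost, narrow version.** The Objective section describes patient costs as those "which will include direct out-of-pocket payments to private health providers (consultations and medications, etc), travel and subsistence costs and productivity losses". The Perspective section adds "While public sector primary healthcare is free at the point of use" and, on payments, "in addition, they may incur costs when using private sector health services". Neither mentions fees paid to public providers.

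**The concern.** A user fee paid to a public hospital is a transfer. It moves part of the bill from the provider to the patient but uses no further resource. If the provider cost is the full cost of delivering the service, adding the patient's fee counts that part of the resource a second time.

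This matters where the arms differ in their use of public services that charge. The Objective section makes changes in referral costs, including emergency and inpatient care, an explicit target, so the place where offsets are sought is also the place where the overlap can arise. If counselling lowers paid hospital use, the saving is exaggerated and the societal ICER looks too favourable. If paid hospital use rises, the bias runs the other way. The societal ICER is offered partly for comparability with other studies, and that comparability suffers if transfers are handled differently.

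**Working it through.** The plan states no figure that depends on this point, so there is nothing to reproduce. The check is an accounting identity, followed by a comparison of the sections.

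**Identity.** For one contact with a public service, let

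- C = provider cost from facility expenditure (Table 1), taken as gross of fee income because no deduction is stated;
- F = fee the patient pays to that public provider (patient-perspective Measurement of resource use);
- O = other patient costs (travel, subsistence, accommodation, time, private fees).

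Plain sum of provider and patient costs: C + F + O.

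Resource cost with the fee treated as a transfer: C + O.

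Excess per paid contact: (C + F + O) − (C + O) = F.

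**Effect on the increment.** Let ΔN be the difference in paid public contacts between the two arms being compared, and ΔE the difference in effect.

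- Excess in societal incremental cost = F × ΔN.
- Excess in societal ICER = F × ΔN / ΔE.

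Both are zero if F = 0 or ΔN = 0. With ΔE positive, the ICER is too low when ΔN is negative and too high when ΔN is positive.

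**Where F can be non-zero.** The Perspective section says public primary care is free, so F = 0 for the counselling, for HIV and diabetes care at the facility, and for public clinic visits. That leaves public services that charge, with hospital ER/OPD and inpatient care as the candidates in Table 1. The document does not say which of these charge, or how much.

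**Scale, by assumption only.** Write f = F/C. The public hospital part of the increment becomes (C + F) × ΔN in place of C × ΔN, a ratio of 1 + f. It is overstated by 0% at f = 0, 5% at f = 0.05, 10% at f = 0.10 and 20% at f = 0.20. These values of f are assumed, not taken from the document. They describe the paid hospital component alone. The effect on the whole societal ICER cannot be computed, because neither fees nor utilisation are given.

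**Sections compared.**

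| Section | Public fees a patient cost? |
|---|---|
| Objective | Not listed; private-provider payments only |
| Perspective | Not listed; private-sector costs only |
| Patient perspective, Measurement of resource use | Yes, captured with private and NGO fees |
| Patient perspective, Valuation of costs | Silent on all user fees |
| Determining cost-effectiveness | Patient costs added to provider costs, no exclusion |

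The silence of the valuation section does not settle the matter. It is equally silent on private fees, which the Objective section plainly includes.

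**The case against.** The strongest reply is that no sentence says public fees enter the societal total. The questionnaire passage describes what is collected, while the sections that define patient cost name private payments only. On that reading public fees are collected but never summed, and nothing is counted twice. This part stands: a reader might infer that the plan definitely counts public fees twice, and the text does not go that far. It does not remove the point, because the list in the Objective section is not worded as exhaustive, the wider wording sits under the patient-perspective costing heading, and nothing takes public fees out of the patient cost that is later added.

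A second reply is that public care is free. That holds for primary care, and so for most of the costing. The document does not extend the statement to hospital or emergency care. Equally, it does not say that these patients pay hospital fees.

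A third is that netting transfers is routine detail that an article leaves to the full analysis plan. Had the article been silent, that would answer the point. But it states the fee items, the valuation basis and the sum itself, and its sections disagree.

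A fourth is that little depends on it. A reader might infer that the cost-effectiveness decision is biased. The document does not support that: the decision rule and threshold comparison use the provider perspective, patient costs are also reported separately, and the societal ICER is an additional presentation.

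**Conclusion.** The point holds in a limited form. Taken together, the stated rules would count any fee paid to a public provider twice in the societal ICER, and the Objective and Perspective sections conflict with the patient-perspective measurement section on whether such fees belong in patient cost at all.

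The effect on the increment is F × ΔN. Its size is unknown, and it is zero if no fee is paid or if paid public contacts do not differ between arms. It is confined to public services that charge. The provider-perspective ICER does not change.

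The conclusion rests on two assumptions: that facility expenditure is gross of fee income, and that public fees captured by the questionnaire are part of the patient cost that is summed. If either is false, the double count disappears, but the inconsistency between sections remains. The point is worth correcting before analysis, but it does not threaten the main economic conclusion.

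**What to change.** Reconcile the Objective and Perspective sections with the patient-perspective Measurement of resource use section, so that all three say the same about public user fees. Then add one sentence to the analysis section: fees paid to public providers are shown in the separately reported patient costs, but are excluded from the societal total (or, equivalently, deducted from provider cost before the two are added). Fees to private, NGO, traditional and faith-based providers, together with travel, subsistence, accommodation and time, are still added.

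The cost is a few words of text. The one practical condition is that public fees can be separated from private and NGO fees in the data. The article lists the types of provider covered but does not say that amounts are recorded separately for each. If they are not, the questionnaire needs that split.

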### Time horizon and discount rate

As the health consequences of the intervention will be experienced over a period extending longer than 1 year, a discount rate will be applied to reflect differentials in timing.^36^ A 3% discount rate will be used for discounting both costs and outcomes to allow comparability with other CEAs.^37^

### Estimating intervention effects

Single study-based estimates of clinical effectiveness will be obtained from the trial, which will provide the primary and secondary outcome measures previously described. In addition to the disease-specific primary outcomes, and the secondary HIV and diabetes outcomes which will be applied in the CEA, the QALY will also be calculated as an end point that will be used in the CUA. The ICER resulting when using a QALY measure represents the additional cost associated with accruing another QALY as one compares strategies (ie, the incremental cost per QALY gained). The QALY allows comparison of ICERs across different diseases and interventions.^37^ QALYs are calculated by multiplying the length of time in a health state by the HRQoL of the health state. The EQ-5D is the most widely used instrument for measuring HRQoL for CUAs.^34^ In South Africa, it has been validated and translated into Afrikaans and isiXhosa, two of the country’s official languages.^38^ The EQ-5D is a self-assessment of health status across five domains which include mobility, self-care, usual activities, pain and discomfort and anxiety/depression.^39^ In this study, the EQ-5D-3L^34^ will be used to measure HRQoL. A single summary index score will be generated using preference weights derived from a time trade-off (TTO)-based valuation survey conducted in Zimbabwe in addition to the commonly used UK value set; the TTO is the most common valuation technique used in LMICs.^40^ As the EQ-5D will be administered at all the assessment intervals (baseline, 6 months and 12 months post-enrolment), there will be three observations of the EQ-5D scores for each patient in the trial. The QALY gained per patient over the trial period will be calculated by measuring the area under the quality of life curve.^37^

### Estimating costs for the provider’s perspective

Within economic evaluation, the appropriate scope of provider costs includes all costs incurred within the intervention and any changes in broader health system costs that can be attributable to the intervention. We have categorised these costs as intervention costs, HIV and diabetes service costs and other related provider costs. As shown in table 1, our approach to estimating these costs entails the measurement of quantities of resources that are used, and multiplying these quantities by the value (or unit cost) of each resource. These separate steps of measurement and valuation are described below.

**Table 1 T1:** Measuring and valuing provider costs

Cost component	Measurement		Valuation	
	Resources used	Quantities or utilisation	Valuation data	Allocation factor
Intervention				
Capital costs				
Facility readiness workshops	Number of staff	Time from trial data	Cost of employment converted to annual equivalent cost	DED/DES/TAU headcount
Intervention training for counsellors	Number of counsellors	Time from trial data	Cost of employment converted to annual equivalent cost	DED/DES/TAU headcount
Counselling room	Space	Square metres	Replacement value converted to annual equivalent cost	DED/DES/TAU headcount
Furniture and equipment	Tape recorders	Inventory	Replacement value converted to annual equivalent cost	DED/DES/TAU headcount
Vehicles	Vehicles	Inventory	Replacement value converted to annual equivalent cost	DED/DES/TAU headcount
Recurrent costs				
Counselling personnel	Number of staff (lay counsellors; registered counsellors; clinical psychologist)	Time from time and motion tool	Cost of employment×proportion of time	DED/DES/TAU headcount
Counselling supplies	Manuals, notebooks, pens	Number used—from trial data	Market value	DED/DES/TAU headcount
Non-intervention personnel	Number of staff	Time from facility data	Cost of employment×proportion of time	Facility headcount
Utilities	Electricity, water, other utilities, phone, cleaning, transport and stationery	Facility utilisation	Annual facility expenditure	Facility headcount
HIV/Diabetes service				
Capital costs				
Buildings	Space used for HIV/diabetes service	Square meters	Replacement value converted to annual equivalent cost	HIV/Diabetes headcount
Equipment and furniture	Equipment and furniture used for HIV/diabetes service	Inventory	Replacement value converted to annual equivalent cost	HIV/Diabetes headcount
Vehicles	Vehicles used for HIV/diabetes service	Inventory	Replacement value converted to annual equivalent cost	HIV/Diabetes headcount
Recurrent costs				
HIV/Diabetes personnel	Number of staff and staff time spent on HIV/diabetes service	Time from facility data	Cost of employment ×proportion of time	HIV/Diabetes headcount
Drugs	ARV/Diabetes medication	Treatment protocol	National tender prices	Direct allocation
Diagnostic tests	CD4 test, diabetes monitoring tests, etc	Treatment protocol	National Health Laboratory Service prices	Direct allocation
Non-HIV/diabetes personnel	Managerial, cleaning and security staff	Facility utilisation	Facility expenditure	Facility headcount
Building operating and maintenance	Electricity, water, other utilities, phone, cleaning, transport and stationery	Facility utilisation	Facility expenditure	Facility headcount
Other related healthcare providers				
Public clinic visit	Average cost per visit	Patient interviews	Facility expenditure	Facility headcount
Public hospital ER/OPD visit	Average cost per OPD visit	Patient interviews	Facility expenditure	Facility Inpatient days and Outpatient headcount
Public hospital inpatient day	Average cost per inpatient day	Patient interviews	Facility expenditure	Facility Inpatient days and Outpatient headcount

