Establishing the use of referral services is challenging given that there is no health information system that enables patient pathways through care to be established. Therefore, to establish patient utilisation of health services beyond their HIV and diabetes care at the primary level, we will administer a patient questionnaire developed for the study at baseline, and at the 6-month and 12-month assessments. Using this questionnaire, we will capture health service utilisation for other primary care services (eg, TB treatment), hospital services, emergency department care, paramedic care and referrals to mental health providers. Patients will be asked to quantify the number of these additional visits, and lengths of stay in hospital. Given concerns with patient recall, we have asked patients to estimate their usage of ambulatory services over the previous month and have used a recall period of 6 months for inpatient services. These data will then be extrapolated to estimate costs over the time horizon.

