#### Valuation of costs

Once the utilisation of services has been established, we will estimate the unit cost of each service. This involves sourcing a value for each item (eg, annual cost of employment multiplied by proportion of time spent), as well as an allocation factor (eg, annual facility head count) allowing the estimation of a unit cost (cost of employment×proportion of time/headcount). These sources of data and allocation factors are outlined in detail in table 1.

For capital items, costs will be estimated using the replacement value method.^37^ In essence, the current replacement value of each items is calculated and annuitized using data on the estimated useful life of the item and an interest rate representing the opportunity cost component for capital, in order to estimate an equivalent annual cost. An estimated useful life of between 5– and 20 years for furniture and buildings will be applied as while an interest rate of 8% will be used as the annuitization factor based on the rate of return on government bonds in South Africa.^37^

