#### Sensitivity analyses

The decision analytical models will allow for univariate and multivariate sensitivity analyses to be conducted. This will enable the robustness of study findings to be tested by varying key parameters such as utilisation rates and assessing the impact on cost-effectiveness results. Standard areas of analytical focus will be considered, including testing sensitivity around the resource cost and prices, and theoretical controversies,^49^ for example, TTO weights^50^ and discounting of outcomes.^36^ Further analyses to inform the economics of task-sharing will include sensitivity analysis focused on economies and diseconomies of scale and scope, using detailed data from the TMT.^51^ This will include testing variations in staff hours worked, variations in staff mix, lay counsellor funding models and infrastructure investments. The impact of intervention dosage on outcomes will also be assessed in the sensitivity analyses. Statistical methods including multiple imputation will be used to manage the effect of missing information on costs and effects.^52^ These sensitivity analyses are summarised in table 2. Probabilistic sensitivity analysis (which allows application of CIs to point estimates) will be used for sensitivity analyses of all relevant individual-level variables. The sensitivity analyses will be used to produce a cost-effectiveness acceptability curve.

**Table 2 T2:** Planned sensitivity analyses

	Base case	Range
Simple sensitivity analysis		
Discount rate	3%	0%–10%
QALYs: HRQoL weights	EQ-5D valued using UK TTO	EQ-5D valued using Zimbabwe TTO
Unit costs	Primary data and data from published sources and official statistics for South Africa	Varied within plausible ranges as determined from a literature review of South African cost studies
Missing data	Multiple imputation	Complete case analysis
Probabilistic sensitivity analysis		
Intervention utilisation data	Mean value	95% uncertainty interval
Referral service utilisation data	Mean value	95% uncertainty interval
EQ-5D/CES-D/AUDIT data	Mean value	95% uncertainty interval
Clinical outcomes (HbA1c, HIV-1 RNA)	Mean value	95% uncertainty interval

AUDIT, Alcohol Use Disorder Identification Test; CES-D, Centre for Epidemiological Studies scale on Depression; EQ-5D, EuroQol-5D; HbA1c, haemoglobin A1c; HRQoL, health-related quality of life; QALY, quality-adjusted life year; TTO, time trade-off.

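### Table 1 values emergency-room and outpatient visits at one outpatient average, so the emergency department offset in the first objective may be mis-valued; paramedic care is counted but has no unit cost

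*Protocol article*

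**What the plan says.** The first objective (MIND economic evaluation, Objective) includes cost offsets from "changes to the costs of referral care (including tuberculosis (TB), emergency department and inpatient care"). Emergency department care is thus a named part of what is to be estimated.

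Under the provider's Measurement of resource use, the patient questionnaire is to capture, among other services, "hospital services, emergency department care, paramedic care and referrals to mental health providers". Emergency department care and paramedic care are listed as separate items, and patients are asked for the number of visits.

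The costing rule under Estimating costs for the provider's perspective is to measure resource quantities, "multiplying these quantities by the value (or unit cost) of each resource". The same section puts attributable changes in wider health system costs within the provider scope.

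In Table 1, the block for other related providers has three rows: a public clinic visit, a "Public hospital ER/OPD visit" and a public hospital inpatient day. The middle row is valued at "Average cost per OPD visit", from facility expenditure, with "Facility Inpatient days and Outpatient headcount" as allocation factor. No ER unit cost, ER headcount or paramedic row appears. On data sources and allocation factors, Valuation of costs states: "These sources of data and allocation factors are outlined in detail in table 1".

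Table 2 plans a sensitivity analysis in which unit costs are "Varied within plausible ranges as determined from a literature review of South African cost studies". It does not single out ER costs.

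**The concern.** The objective and the questionnaire treat emergency department care as distinct, but the valuation table gives it no price of its own. Two consequences follow.

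First, with one shared unit cost, a one-for-one move from an ER visit to an OPD visit has a cost effect of exactly zero, whatever the true prices are. Replacing emergency attendance with planned attendance is one plausible route to a cost offset, and the table as written cannot show it. Where ER visits rise or fall without such a substitution, the change is priced, but at an outpatient value that may be wrong.

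Second, paramedic contacts are collected and fall within the stated provider scope, yet the table that lists the valuation sources has nothing to multiply them by.

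Under Determining cost-effectiveness, the provider-perspective incremental cost per QALY is compared with a threshold. Any error in the between-arm difference in these costs passes into that ratio.

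**Working it through.** The document states no unit costs or visit counts, so there is no figure to reproduce. The check has a textual part and an illustrative part.

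**Textual check**

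| Item | First objective | Questionnaire | Table 1 |
|---|---|---|---|
| Emergency department visit | Named | Listed separately | Shares a row with OPD, at the OPD average |
| Paramedic care | Not named | Listed separately | No row |
| Inpatient care | Named | Hospital services, length of stay | Own row (inpatient day) |

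**Illustrative arithmetic**

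Inputs, all assumed because the document gives none:
- true OPD visit cost = 1 (the unit of account)
- true ER visit cost = k, taken from 0.8 to 3
- share of ER visits in the visits that form the OPD average = s, taken as 0 (no pooling) or 0.3

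Formulas:
- unit cost applied to both visit types: u = 1 + s(k - 1)
- relative error in the value of an ER visit gained or avoided: u/k - 1
- relative error in the value of an OPD visit: u - 1
- true cost difference between an ER and an OPD visit: k - 1; difference under Table 1: u - u = 0

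| k | s | u | ER error, u/k - 1 | OPD error, u - 1 | True ER-OPD difference, k - 1 |
|---|---|---|---|---|---|
| 0.8 | 0 | 1.00 | +25% | 0% | -0.2 |
| 1 | 0 | 1.00 | 0% | 0% | 0 |
| 1.5 | 0 | 1.00 | -33% | 0% | 0.5 |
| 2 | 0 | 1.00 | -50% | 0% | 1 |
| 3 | 0 | 1.00 | -67% | 0% | 2 |
| 1.5 | 0.3 | 1.15 | -23% | +15% | 0.5 |
| 2 | 0.3 | 1.30 | -35% | +30% | 1 |
| 3 | 0.3 | 1.60 | -47% | +60% | 2 |

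For example, with k = 3 and s = 0.3, u = 1 + 0.3 × 2 = 1.6. The ER error is 1.6/3 - 1 = -47% and the OPD error is +60%.

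**Effect of the planned sensitivity analysis**

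Multiply the shared value by any factor c. ER and OPD visits are then both priced at cu, and the difference between them is cu - cu = 0 for every c. Varying the row's single value changes the size of an offset from fewer visits overall, but never the zero assigned to a substitution. The probabilistic analysis in Table 2 varies referral utilisation, which is a quantity and not a price ratio. Neither analysis supplies a unit cost for an item that lacks one.

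**The case against.** The strongest case on the other side has five parts.

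1. **No error is demonstrated.** ER and OPD costs might be equal, or ER might be cheaper. This stands. A reader might infer that the ER offset is understated by a third to two thirds. The document does not support that, because those percentages rest on an assumed ratio of 1.5 to 3, and the sign reverses below 1.

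2. **The row may be a pooled ambulatory average.** Its label covers both visit types, and expenditure is allocated top-down with no ER headcount. This is a fair reading, and under it the no-pooling figures are the extreme case. It does not rescue the row: pooling shrinks the ER error but moves some of it onto OPD visits, and a switch is still priced at zero.

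3. **Paramedic care may be valued elsewhere.** Table 2 allows published sources and official statistics for base-case unit costs, and an article condenses a fuller costing plan. So the claim that paramedic care certainly enters at zero goes too far. What stands is that the article calls Table 1 the detailed list, and the table omits this item. Nor should the omission be tied to the emergency offset in the first objective, which names emergency department care and not paramedic care. The paramedic gap is between the questionnaire and the table.

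4. **Materiality is unknown.** No visit rates are given, and the Discussion expects staff time to be among the main cost drivers. This also stands. It would be wrong to infer that the plan can show no saving from fewer emergencies: an avoided ER visit still saves u, and a move to a public clinic visit is priced on a different row. Only a one-for-one ER-to-OPD switch nets to zero.

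5. **A single average for hospital ambulatory care is ordinary gross costing.** It is acceptable as a base case, but it fits poorly with an objective that singles out emergency department costs, and the article neither justifies the proxy nor tests it.

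**Conclusion.** The point holds in a limited form. Table 1 states a valuation rule that prices ER and OPD visits identically, although the first objective names emergency department cost changes. The zero cost effect of a one-for-one switch follows from the rule itself and needs no assumption. How far other ER offsets are mis-valued is unknown: across the assumed ratios of 0.8 to 3, the error runs from +25% to -67% without pooling, and is zero if the two visit types cost the same. The effect on the cost-effectiveness ratio also depends on between-arm differences in ER visits, which cannot be judged from the document.

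Separately, paramedic care is collected and is within the provider scope, but has no unit cost in Table 1. If the table is applied as written, all of any change in its cost is left out of provider costs. Whether a fuller costing plan values it cannot be seen from the article.

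Both points should be corrected before the cost analysis, because the remedy is cheap.

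**What to change.** **ER visits.** Either:
- split the shared row, giving ER visits their own unit cost: facility ER expenditure over ER headcount where the two can be separated, otherwise a published South African cost; or
- keep the shared value as base case, state whether the average includes ER visits, and add the ER:OPD cost ratio to the unit-cost sensitivity analysis in Table 2, so that the two prices can move apart.

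**Paramedic care.** Add a Table 1 row with a published or tariff unit cost.

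**Cost.** A table edit and two unit costs. No new patient data are needed, since the questionnaire already lists both services and asks for visit numbers. The small downside is that some facilities cannot separate ER expenditure, so a published cost must be used there.
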